## Abstract

**Background:** Cardiovascular disease is a major global health concern and prevalence is high in adults with obstructive sleep apnea (OSA). Lowering blood pressure (BP) can greatly reduce cardiovascular disease risk and physical activity is routinely prescribed to achieve this goal. Unfortunately, many adults with OSA suffer from fatigue, daytime sleepiness, and exercise intolerance—due to poor sleep quality and nocturnal hypoxemia—and have difficulty initiating and maintaining an exercise program. High-resistance inspiratory muscle strength training (IMST) is a simple, time-efficient breathing exercise consistently reported to reduce BP in small, selective groups of both healthy and at-risk adults. Herein we present the study protocol for a randomized clinical trial to determine the long-term efficacy of IMST performed regularly for 24 weeks in middle-aged and older adults with OSA. The primary outcome is casual systolic BP. Secondary outcomes are 24-h systolic BP and circulating plasma norepinephrine concentration. Other outcomes include vascular endothelial function (endothelial-dependent and -independent dilation), aortic stiffness, casual and 24-h diastolic BP, and the influence of circulating factors on endothelial cell nitric oxide and reactive oxygen species production. Overall, this trial will establish efficacy of high-resistance IMST for lowering BP and improving cardiovascular health in middle-aged and older adults with OSA.

**Methods:** This is a single-site, double-blind, randomized clinical trial. A minimum of 92 and maximum of 122 male and female adults aged 50–80 years with OSA and above-normal BP will be enrolled. After completion of baseline assessments, subjects will be randomized in a 1:1 ratio to participate in either high-resistance or sham (low-resistance) control IMST, performed at home, 5 min/day, 5 days/week, for 24 weeks. Repeat assessments will be taken after the 24-week intervention, and after 4 and 12 weeks of free living.

**Discussion:** This study is designed to assess the effects of 24 weeks of IMST on BP and vascular function. The results will characterize the extent to which IMST can reduce BP when performed over longer periods (i.e., 6 months) than have been assessed previously. Additionally, this study will help to determine underlying mechanisms driving IMST-induced BP reductions that have been reported previously.

**Clinical Trial Registration:** This trial is registered with ClinicalTrials.gov (Registration Number: NCT04932447; Date of registration June 21, 2021).

## Introduction

### Background and Rationale

Cardiovascular disease (CVD) is the leading cause of death in the US and worldwide (1, 2). Obstructive sleep apnea (OSA) is a chronic sleep-related breathing disorder, characterized by repeated partial (hypopnea) or complete (apnea) collapse of the pharyngeal airway, with higher-than-average rates of CVD (3). OSA prevalence has risen sharply over recent decades (4), with current estimates indicating one billion adults (ages 30–69 years) are affected worldwide and prevalence rates in the US nearing 48% (5).

From a physiological perspective, airflow limitation and obstructions often result in chronic intermittent hypoxemia, arousal from sleep, and bursts of sympathetic activity that provoke surges in blood pressure (BP) and heart rate (6–9). In turn, chronic intermittent hypoxemia promotes reactive oxygen species (ROS) overproduction and contributes to chronic systemic inflammation (10, 11). The health implications are especially profound for older adults (65+ years of age) regardless of OSA status, as over 80% of all cardiovascular deaths occur in this age group (12). Age-related stiffening of the large elastic arteries (i.e., aortic and carotid) (13–16) and vascular endothelial dysfunction compound the problem.

The primary therapy for OSA is continuous positive airway pressure (CPAP), which delivers a steady stream of pressurized air *via* a mask that stents the airway, preserving airflow and oxygenation. CPAP is highly efficacious among adherent users (≥4 h/night, 5 nights a week) as it normalizes sleep architecture (17, 18), reduces sympathetic nervous system activity (19, 20) and lowers systolic BP (SBP) (2–6 mmHg) (21, 22). Despite enhanced usability, CPAP adherence rates remain low (30–60%) (23), with ~50% of patients discontinuing use within the first year (24). Low adherence rates limit the therapeutic impact of CPAP for ongoing CVD and/or CVD development (25–27).

Regular aerobic exercise has important physiologic and clinical benefits in adults with above-normal BP and/or OSA, including reductions in BP (28), OSA severity (29), and risk for adverse cardiovascular events (30, 31). Unfortunately, the salient features of OSA, including obesity (BMI >30 kg/m^2^), excessive daytime sleepiness (32), and lethargy (33–37), render many adults with this disorder unwilling or unable to exercise, or cause them to discontinue exercise before achieving health gains (38, 39). Time availability is a major barrier to exercise adherence (39, 40) and the need to establish the efficacy of novel forms of exercise that are time-efficient, well-tolerated, and effective has never been greater (41, 42).

Among the exercise modalities that offer improved adherence, shorter duration of effort [relative to current guidelines (43)], and BP-lowering effects, is a respiratory training protocol known as inspiratory muscle strength training, or IMST (42). IMST is performed on a portable hand-held device (Figure 1) and entails repeated inspiratory efforts against a resistance. IMST is distinct from more traditional forms of aerobic exercise in that it is performed (a) in stationary sitting or standing, (b) at slower breathing rates (~10–12 breaths/min), and (c) requires large inspiratory (i.e., negative) pressures (44, 45) that exceed those generated in tidal breathing (46), deep breathing (45), or high-intensity aerobic exercise (i.e., 95% VO_2_max) (47, 48). Another key distinction is a very abbreviated training format which, for high resistance IMST, comprises just 30 breaths (5 min/day), or a total training time of ~30 min per week.

**Figure 1 F1:**
[figure not shown]
Handheld POWERbreathe training device.

Over the short-term (i.e., 6 weeks), high-resistance IMST has yielded improvements in SBP, sympathetic nervous system activity, and endothelial function in small groups of healthy and at-risk populations (45, 49–52), including middle aged and older (MA/O) adults with OSA. However, the results for OSA adults are preliminary and require confirmation in a larger group of patients. Furthermore, guidelines issued by the American College of Cardiology and the American Heart Association (ACC/AHA) indicate that non-pharmacological therapies designed to reduce BP should be assessed for efficacy within 3–6 months of treatment initiation (28), and the efficacy of high-resistance IMST administered over the longer-term has yet to be assessed. By extension, it is not known how long IMST-induced BP reductions persist after training cessation. Lastly, in view of evidence that high-resistance IMST improves endothelial function in otherwise healthy MA/O adults with above-normal BP (52), the potential for IMST to induce similar benefits in MA/O adults with OSA warrants assessment.

The CHART (Cardiovascular Health, Apnea, and Respiratory Training) Study is a Phase II clinical trial that seeks to establish the benefits of 24 weeks IMST on: (1) casual (resting) and 24-h (ambulatory) SBP, and (2) to determine if the reductions in SBP are sustained following cessation of IMST. In addition, we seek to understand the underlying mechanisms that drive IMST-related BP reductions. Specifically, we will assess the effects of IMST on: (1) markers of sympathetic nervous system activity and other potential vasoconstrictor factors, arterial stiffness, nitric-oxide (NO)-mediated endothelial function (endothelial-dependent dilation), smooth muscle sensitivity to NO (endothelial-independent dilation), and systemic oxidative stress and inflammation; and (2) the influence of changes in circulating factors on the release of NO and ROS from human umbilical vein endothelial cells *ex vivo*, using a novel cell-culture model. To achieve these objectives, we will assess the effects of high- vs. low-resistance IMST performed at home 5 min/day, 5 days/week, for 24 weeks in adults 50–80 years of age with OSA (apnea-hypopnea index ≥15) and above-normal SBP (≥120 mmHg). Further, we will reassess these measures after 4 and 12 weeks of free-living following cessation of the 24-week training intervention.

## Methods

### Study Design

The CHART Study is a Phase II randomized, double-blind, sham-controlled, mechanistic clinical trial comparing high- and low-resistance IMST in 122 MA/O adults (50–80 years) with OSA. The study is a repeated measures design with assessments at four time points: baseline, post intervention, and at follow-up 4- and 12-weeks post-intervention (Figure 2).

**Figure 2 F2:**
[figure not shown]
Detailed overview of the CHART study protocol. 6MW, six-minute walk; AHI, apnea hypopnea index; BMI, body mass index; BP, blood pressure; CHAMPS, Community Healthy Activities Model Program for Seniors physical activity questionnaire; ESS, Epworth Sleepiness Scale; FMD_BA_, brachial artery flow-mediated dilation; HR, heart rate; IMST, inspiratory muscle strength training; PI_max_, maximal inspiratory pressure; PNE, plasma norepinephrine; PSQI, Pittsburgh Sleep Quality Index; PWV_CF_, carotid-femoral pulse wave velocity; SBP, systolic blood pressure; *Indicates PWV_CF_ and FMD_BA_ will be performed with saline and Vitamin C infusion. ^†^The following surveys will be completed at home: CHAMPS, ESS, PSQI.

### Study Population

Men and women 50–80 years of age with OSA and above-normal BP from all ethnic backgrounds will be eligible to participate. Subjects will be screened to determine whether they meet all the inclusion criteria and have none of the exclusion criteria (Table 1).

**Table 1 T1:** Inclusion and exclusion criteria.

**Inclusion**	**Exclusion**
• Age 50–80 years • Ability to understand study procedures and to comply with them for the entire length of the study • Ability to provide informed consent; • Willing to accept random assignment to condition • AHI ≥15 • Individuals with who are unwilling or unable to adhere to CPAP • Individuals who are adherent to CPAP therapy (i.e., 4 h/night on 70%/nights over 30 days in the first 3 months of initial usage) • Individuals who are adherent to mandibular advancement device each night • Above-normal SBP (i.e., SBP ≥120) • BMI ≤ 40 kg/m^2^ • Weight stable in the prior 3 months (<3.0 kg weight change) and willing to remain weight stable throughout the study • No change in anti-hypertensive medications or other medications (prescription or dosing) in the prior 3 months and willingness to maintain current medication regimen throughout the study • Absence of unstable clinical disease as determined by medical history, physical examination, and blood chemistries • Total cholesterol <240 mg/dL • Fasting plasma glucose <300 mg/dL	• Age <50 or >80 years • AHI <15 • BMI > 40 kg/m^2^ • Individuals with central or mixed sleep disordered breathing • Severe hypoxemia (<80% for >10% of recording time) during sleep • ESS >15 • SBP ≤ 120 or >160 • DBP >100 • Current smoker • Chronic overt and poorly controlled medical condition (e.g., diabetes, chronic kidney disease, cancer, congestive heart failure) • Cheyne-Stokes Respiration • Alcohol or illegal drug dependence or abuse • Uncontrolled thyroid disease or change in thyroid medication within previous 3 months • Regular/vigorous aerobic exercise (> 4 bouts/week, >30 min/bout at high workload >6 METS)

*AHI, apnea hypopnea index; BMI, body mass index; CPAP, continuous positive airway pressure; DBP, diastolic blood pressure; ESS, Epworth Sleepiness Scale; METS, metabolic equivalents; SBP, systolic blood pressure*.

### Outcomes

#### Primary Outcome

##### Casual Systolic Blood Pressure

Casual SBP will be assessed in accordance with ACC/AHA guidelines (28) between 7 and 10 a.m. and after overnight fasting. Subjects will be seated quietly with their back supported, feet flat on the floor, and arms supported on a table at heart level with the palms facing up. SBP will be measured with an automated oscillometric sphygmomanometer (SunTech CT40, SunTech Medical), validated according to standards set by the British Hypertension Society, International Protocol and Association for the Advancement of Medical Instrumentation (53), and calibrated regularly by the manufacturer. Measurements will be performed in triplicate over the brachial artery of the non-dominant arm after at least 5 min of quiet rest and with 1 min of recovery between measures. SBP will be defined as the average of the three pressures, and will be recorded at baseline, weekly throughout the intervention, after the 24-week training period, and at 4- and 12-weeks post-intervention.

#### Secondary Outcomes

##### Twenty-Four-Hour Ambulatory Systolic Blood Pressure

Twenty-four-hour SBP will be assessed with 24-h ambulatory non-invasive BP monitoring. Given the propensity for sleep disturbance/arousal reaction to contribute to elevations of BP, assessments will be continuous, beat-to-beat over a 24-h period with the and European Association of Hypertension validated cuffless monitor (SOMNOtouch, SOMNOmedics Germany) (54). Participants will be given a diary to record any physical or psychological events that occur during the 24-h period that may influence BP. SBP will be averaged over the entire 24-h period at baseline, after the 24-week training period, and at 4- and 12-weeks post-intervention.

##### Daytime and Nighttime Ambulatory Systolic Blood Pressure

Ambulatory SBP data will be broken into daytime (16 h) and nighttime (8 h) segments according to subjects' individual sleep-wake cycles. Mean SBP (mmHg) will be calculated for daytime and nighttime periods to evaluate circadian SBP profile at baseline, after the 24-week training period, and at 4- and 12-weeks post-intervention.

##### Circulating Plasma Norepinephrine

Concentration of circulating PNE (pg/mL) will be determined from venous blood samples acquired following 20 min of supine rest in a quiet, temperature-controlled room. PNE will be quantified *via* high-performance liquid chromatography (55) from blood collected at baseline, after the 24-week training period, and at 4- and 12-weeks post-intervention.

#### Other Outcomes

##### Endothelial Dependent Dilation

EDD will be assessed *via* brachial artery flow-mediated dilation (FMD_BA_) using high-resolution ultrasonography (Canon Xario 200G) (52, 56), the gold-standard *in vivo* measure of conduit artery vascular endothelial function, that is primarily mediated by NO. FMD_BA_ will be assessed by measuring brachial artery diameter and blood velocity at baseline and for 3 min following reactive hyperemia induced by 5 min of forearm blood flow occlusion with a cuff placed on the upper forearm and inflated at least 50 mmHg above SBP.

Data will be expressed as both percent and absolute (mm) change in arterial diameter from baseline (pre-cuff inflation diameter). Shear area-under-the-curve up to peak diameter will be calculated, and if group- or timepoint-differences exist, FMD_BA_ will be adjusted accordingly. Brachial artery diameter and blood velocity will be analyzed offline with commercially available software (Brachial Analyzer, Medical Imaging Applications LLC, Coralville, IA, USA). Peak arterial diameter will be compared to baseline diameter to calculate absolute change (mm) and percent change in diameter in response to the forearm hyperemic stimulus at baseline, after the 24-week training period, and at 4- and 12-weeks post-intervention.

To determine tonic oxidative stress-mediated suppression of endothelial function, FMD_BA_ will be repeated after intravenous infusion of supratherapeutic concentrations of the potent ROS-scavenging antioxidant, Vitamin C, and isovolumic saline infusion, as described previously (57, 58). A bolus of 0.06 g Vitamin C/kg fat-free mass dissolved in 100 mL of saline will be infused by IV at a rate of 5 mL/min for 20 min, followed immediately by a drip infusion of 0.02 g/kg fat-free mass dissolved in 30 mL saline infusion at a rate of 0.5 mL/min. FMD_BA_ will be performed after the bolus dose, during the drip infusion. FMD_BA_ with infusions will be performed at baseline, after the 24-week training period, and at 4- and 12-weeks post-intervention.

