##### Influence of Circulating Factors on Nitric Oxide and Reactive Oxygen Species Production

Using blood drawn from experimental groups we will determine if IMST improves endothelial function *via* changes in circulating factors that increase endothelial cell NO production and/or reduce endothelial ROS production in cultured human umbilical vein endothelial cells (HUVECs) (American Type Culture Collection). We will expose HUVECs *ex vivo*, to media conditioned with serum drawn from participants in each group as described previously (52). After 2–4 passages, HUVECs will be plated in 96-well culture plates and incubated for 24 h at 37°C and 5% CO_2_ in basal media supplemented with 10% subject serum obtain before and after 24 weeks of low-resistance or high-resistance IMST. After incubation, cells will be co-incubated with fluorescent probes DAR-4M AM to detect NO production, and CellROX Deep Red to detect ROS production. Cells imaged with DAR-4M AM will be imaged 5 min after the addition of 200 μmol/L of acetylcholine to the cell culture media to stimulate NO production. Analysis will be done with Image J (National Institutes of Health). Data will be expressed as a fold change in NO/ROS production relative to the baseline timepoint.

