### Statistical Analysis

The same statistical approach will be used to address all hypotheses, as each hypothesis uses data collected on continuous outcomes (e.g., casual and 24-h BP) from a two-arm design with multiple time points. A standard repeated measures (with the number of time points depending on outcome) mixed model analysis of variance will be used to estimate average change from baseline within arms. Models will adjust for stratification on OSA severity, sex, and age. Subject specific random effects will be used to account for the repeated measures on an individual. Inferences will be based on available data using maximum likelihood, which accommodates data missing at random. We propose a within-individual analysis for the study (comparisons between arms will be based on average change from baseline vs. average at endpoint) as the correlations between baseline and 6-week SBP and plasma norepinephrine in our preliminary data were ~0.60 or larger (49). Effect sizes and confidence intervals will be reported in addition to *p*-values. Unless otherwise mentioned, tests will be two-sided and conducted at the 5% significance level.

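### FMD is shear-adjusted only if shear is seen to differ, so its estimand is not fixed; NO/ROS fold change, read as own-baseline, does not suit the stated repeated-measures model.

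*Protocol article*

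**What the plan says.** **FMD.** The adjustment rule under Endothelial Dependent Dilation is conditional: "Shear area-under-the-curve up to peak diameter will be calculated, and if group- or timepoint-differences exist". Where that condition is met, the FMD values are corrected for it. FMD is measured without infusion, with saline and with vitamin C. The adjustment sentence does not say whether one decision covers all three conditions.

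**NO and ROS.** Endothelial cells are exposed to "subject serum obtain before and after 24 weeks of low-resistance or high-resistance IMST", so there are two time points. The scale is stated: "Data will be expressed as a fold change in NO/ROS production relative to the baseline timepoint".

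**Model.** The Statistical Analysis section opens with "The same statistical approach will be used to address all hypotheses". It then specifies: "A standard repeated measures (with the number of time points depending on outcome) mixed model analysis of variance will be used to estimate average change". The change meant is the one since baseline, taken separately in each arm. On correlation between visits it says "Subject specific random effects will be used to account for the repeated measures on an individual". The covariate rule reads "Models will adjust for stratification on OSA severity, sex, and age". The section on randomization adds CPAP and treatment-by-CPAP terms. Estimation is by maximum likelihood on available data, and arms are compared on average change from baseline. Shear is not among the listed covariates, and no separate model is named for a ratio outcome. The hypotheses listed under Other Hypotheses include NO-mediated dilation and ex vivo ROS production, so this model covers both.

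**The concern.** Shear after training is a post-randomisation variable that the training may change. If FMD is adjusted exactly when shear differs, a pre-test on observed data chooses between two effects: the total effect on FMD, and the effect that does not run through shear. The reader cannot know in advance which one will be reported. When the arms do differ in shear, any benefit acting through shear is removed. If the trigger fires for one infusion condition and not another, the vitamin C contrast could set adjusted against unadjusted FMD.

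Fold change relative to a participant's own baseline turns every baseline into the constant 1. A repeated-measures model with a subject random effect expects the baseline to be a measured, variable quantity. The mean of a ratio also exceeds 1 when nothing has changed. That would favour an apparent rise in NO and mask part of a fall in ROS within an arm.

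The trial describes itself as mechanistic, and these outcomes supply part of its mechanistic evidence.

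**Working it through.** **Inputs from the article:** 45 completers per arm, effect size 0.63, two-sided 5%, 46–61 randomised per arm, 75% retention (stated in the sex-specific calculation), and a baseline to follow-up correlation of about 0.60 or larger (stated for SBP and norepinephrine only). **Assumed, because the article gives none for these outcomes:** CV 0.2–0.5 and r 0.3–0.8 for log-normal NO/ROS; shear–FMD slope 0.3–0.7; a 0.5 SD shear difference between arms; a direct FMD effect of 0.30 SD.

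**Plan's own figure.** Power at 45 per arm: Φ(0.63 × √(45/2) − 1.96) = Φ(2.99 − 1.96) = Φ(1.03) ≈ 85% by the normal formula, and 84.0% by the t-test. The stated figure of over 80% is reproduced.

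**(a) Shear rule** (simulation, 45 per arm, trigger = shear p < 0.05 by group or by time point)
- No true effect on shear or FMD: the rule triggers in about 10% of trials (1 − 0.95² = 9.75%). Type I error is 3.5–4.5%, so it is not inflated.
- Shear differs by 0.5 SD: the group test alone triggers with probability Φ(0.5 × 4.74 − 1.96) = Φ(0.41) ≈ 66%. Adding the time-point test brings this to about 87%.
- Total effect = 0.30 + 0.5 × slope, which is 0.45, 0.55 and 0.65 SD for slopes of 0.3, 0.5 and 0.7. The direct effect stays at 0.30 SD.
- At slope 0.5 the mean estimate is 0.55 never adjusted, 0.31 always adjusted and 0.32 under the conditional rule.
- Over slopes 0.3–0.7 the chance of significance moves from 56–86% to 31–51%. These are chances of detecting two different effects.

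**(b) Fold change, own-baseline reading**

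Mean fold with no true change is exp(s²(1 − r)), with s² = ln(1 + CV²):

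| CV | s² | r = 0.8 | r = 0.6 | r = 0.3 |
|---|---|---|---|---|
| 0.2 | 0.039 | 1.01 | 1.02 | 1.03 |
| 0.3 | 0.086 | 1.02 | 1.04 | 1.06 |
| 0.5 | 0.223 | 1.05 | 1.09 | 1.17 |

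Power for a 15% effect at CV 0.3, r 0.6, 45 per arm:
- Log ANCOVA: residual SD = 0.294 × √(1 − 0.36) = 0.235. SE = 0.235 × √(2/45) = 0.0495. ln(1.15)/SE = 0.140/0.0495 = 2.82. Power = Φ(0.86) ≈ 80%.
- t-test on fold change (simulation): 69%. As a cross-check, log change has SD 0.294 × √(2 × 0.4) = 0.263 and SE 0.0554, so z = 2.52 and power ≈ 71%.

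Type I error of the stated mixed model on fold change:
- All baseline residuals are zero, and the estimated random-intercept variance was 0 in every simulated run. The pooled residual variance is then 45v/(n + 45), where n is the number of baseline rows per arm and v the variance of the fold. The variance of the change in one arm becomes 45v/(n + 45) × (1/n + 1/45) = v/n. The correct value is v/45.
- With n = 45 (complete data) the two agree. Simulated type I error is 5.6%, the same as for raw log data.
- With n = 61 randomised and 45 completing (61 × 0.75 ≈ 45), the SE is too small by the factor √(45/61) = 0.859. Type I error = 2 × (1 − Φ(1.96 × 0.859)) = 9.2%. Simulation gives 10.6%. The same model on log values gives 5.2%.
- A plain between-arm t-test of fold change keeps its level (4.2–5.3%).

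**The case against.** **Shear is the stimulus of the FMD test.** If the target is endothelial function for a given stimulus, removing a stimulus difference may be intended. That stands as an argument for reporting shear-adjusted FMD. It does not justify letting a pre-test decide when to do so.

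**Shear fits the model.** Shear could enter the mixed model as a time-varying covariate, so it is unlisted rather than incompatible. The test, threshold and adjustment method may sit in an analysis plan not shown, and their absence is not raised here. The conditional trigger itself is stated in the article.

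**False positives.** A reader might infer that the shear rule inflates type I error, or that the fall in the chance of significance is a pure loss of power. Neither is supported. Null type I error is 3.5–4.5%, and the fall compares the total effect with the direct effect under assumed inputs.

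**Invalid model.** A reader might also infer that a fold-change analysis cannot be valid. That goes too far. A between-arm test keeps its level, the complete-data mixed model gives 5.6%, and with no treatment effect the upward bias is the same in both arms and cancels between them. The 9–11% error arises only if participants without a post-training value still contribute a baseline row of 1. Maximum likelihood on available data permits this, but the article does not say it will be done for this outcome.

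**Wording.** The article refers to the baseline time point, not to each participant's own baseline, and says how data are expressed rather than modelled. Own-baseline is the natural reading. Under a group reference or a display-only scale, most of (b) falls away.

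**Conclusion.** The point holds in limited form and is worth correcting.

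(a) The FMD estimand is not fixed. Under the assumed 0.5 SD shear difference, most trials (about 87%) would report the shear-independent effect in place of the total effect: 0.32 against 0.55 SD at slope 0.5. The defect is an estimand that depends on the data, not false positives.

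(b) On the own-baseline reading, fold change does not suit the stated model. The costs are a small upward bias in the within-arm mean (about 2–6% at CV 0.3, up to 17% at CV 0.5), a loss of between-arm power (about 69% against 80% in one scenario), and a type I error of about 9–11% only if dropouts' baseline rows are kept.

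The CVs, shear shift, slopes and effect sizes are assumptions, as is the correlation for NO and ROS. Only outcomes listed under Other Outcomes are affected. Casual SBP, 24-h SBP and plasma norepinephrine are untouched, and norepinephrine, arterial stiffness and sympathetic nerve activity also address mechanism, so it would be wrong to infer that all mechanistic conclusions rest on this.

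**What to change.** - **FMD:** delete the condition that differences must exist. Name unadjusted FMD as the main analysis and always report shear-adjusted FMD alongside it, whatever the shear comparison shows. Apply the same rule to the no-infusion, saline and vitamin C conditions.
- **NO and ROS:** analyse the log signal with the measured log baseline in the model, and report the between-arm ratio of geometric means with its confidence interval. Use fold change for display only.

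Settle both before unblinding. The cost is analysis wording and one extra table. Shear and the NO and ROS signals at both time points are measured under the existing plan, so no new data are needed.
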